## Abstract

**Background:**

Symptoms of anxiety and depression are common in childhood, as are risk factors that undermine wellbeing: low self-esteem and limited participation in daily occupations. Current treatments focus primarily on modifying internal cognitions with insufficient effect on functional outcomes. Occupational therapists have a role in measuring and enabling children’s functional abilities to promote health and wellbeing. To-date there is no evidence for the use of occupational therapy as an intervention to promote mental health or increase self-esteem, participation and wellbeing in a preventative context. The aim of this cluster-randomised controlled study is to investigate the effectiveness of an 8-week occupational therapy group intervention (Kia Piki te Hauora) at reducing symptoms of anxiety and depression and improving self-esteem, participation and wellbeing in children aged 11–13 years.

**Methods/design:**

In this two-arm, pragmatic, cluster-randomised controlled trial, 154 children will be recruited from 14 schools. All mainstream schools in the region will be eligible and a convenience sample of 14 schools, stratified by decile ranking (i.e. low, medium, and high) will be recruited. Eight to twelve students aged 11–13 years from each school will be recruited by senior school personnel. Following consent, schools will be randomised to either the intervention or waitlist control arm of the trial. The study will employ a parallel and one-way waitlist-to-intervention crossover design. Each cluster’s involvement will last up to 19 or 31 weeks depending on allocation to the intervention or waitlist respectively. The primary outcome is symptoms of anxiety and secondary outcomes are symptoms of depression, self-esteem, participation in daily occupations and wellbeing. Outcome measurement will be repeated at baseline, post-intervention and again at 8–9 weeks follow-up. Planned statistical analyses will utilise repeated measures analysis of covariance. The primary analysis will be based on an intention-to-treat analysis set and include only parallel data. The crossover data will only be used in secondary analyses.

**Discussion:**

This is the first cluster-randomised controlled trial to investigate an occupational therapy intervention promoting emotional wellbeing in a non-clinical sample of children. Results will contribute to the limited evidence base for occupational therapists in this field and potentially support investment in these services.

**Trial registration:**

Australia/New Zealand Clinical Trials Register: ACTRN12614000453684.

## Background

Up to 10.5% of children aged 10–14 years reportedly experience anxiety that produces unhelpful internal cognitions and impacts on their participation in occupations, level of functioning and development (Costello et al.,
2003; Zahn-Waxler et al.,
2000). A significant relationship between anxiety and depression has been clearly identified (Costello et al.,
2003; Silverman & Treffers,
2001) with anxiety disorders in childhood and adolescence shown to precede and predict later depressive disorders (Merrick,
1992; Zahn-Waxler et al.,
2000). Consequently, the need for early intervention is vital (Friedberg et al.,
2000).

Anxiety, participation and functioning are closely related. A child with symptoms of anxiety may present with numerous worries that may seem disproportionate or more pervasive than those expressed by their peers; they may be restless, easily fatigued, have difficulty concentrating or be reluctant to participate in the same activities as their peers (American Psychiatric Association,
1994). Participation can be defined as ‘involvement in a life situation’ or meaningful occupation, such as school or play (World Health Organization,
2007, p. 9). Merrick (
1992) found increased mental wellbeing in children was related to increased levels of participation in occupations and Krupa et al. (
2003) reported an imbalance in occupational participation created an increased risk for wellbeing and the onset of mental ill-health. Functioning, as defined by the World Health Organization (WHO) is a combination of the body’s physiological and anatomical structures and the ‘execution of a task or action by an individual’ that impact on an individual’s ability to participate in life situations (World Health Organization,
2007). Despite this well-documented relationship between anxiety, participation and functioning, evidence for interventions directly targeting functioning and participation, rather than cognitive processing errors alone, is limited (Vitiello et al.,
2006).

We reviewed published experimental research that explored the range of preventative mental health interventions available for children (aged 7–19 years) in the school environment. The majority of interventions described demonstrated the effectiveness of Cognitive Behaviour Therapy (CBT) at modifying an individual’s internal cognitions (Bernstein et al.,
2005; Dadds et al.,
1997; Horowitz et al.,
2007; Pössel et al.,
2005). However, CBT has been found insufficient in effecting significant change when level of functioning was measured as an outcome (Vitiello et al.,
2006).

Other common interventions reported were building social networks and skills for help-seeking (Aseltine & DeMartino,
2004; Eggert et al.,
2002; Thompson et al.,
2001) and developing life skills (Eggert et al.,
2002; Thompson et al.,
2001). A few studies reported interventions based on Interpersonal Therapy (Horowitz et al.,
2007), physical activity (Bonhauser et al.,
2005), and information processing (Pössel et al.,
2005). All of the interventions reviewed were conducted with students in groups and ranged in duration from 1 to 2 hours per week over a period of 8 to 12 weeks. In all studies reviewed the intervention group was compared to a control group, with some studies also including comparisons to an alternative intervention or an attention-control group also (Bernstein et al.,
2005; Eggert et al.,
2002; Horowitz et al.,
2007; Thompson et al.,
2001). Most studies explicitly reported the use of cluster randomisation and a few indicated randomisation occurred at the individual level (Aseltine & DeMartino,
2004; Bonhauser et al.,
2005; Horowitz et al.,
2007). All studies reviewed involved repeated measures with an explicit or implied intention-to-treat approach to analysis. Blinding was not fully described for any of the studies; however some reported outcome assessors being blinded to condition allocation (Bernstein et al.,
2005; Dadds et al.,
1997; Horowitz et al.,
2007) and many referred to preventing contamination between conditions. Nomination by a teacher was a common method for identifying participants.

General conclusions from these studies indicated experimental interventions were more effective at reducing the rates of symptoms of concern than control interventions; in the latter, symptoms typically increased (Dadds et al.,
1997). Strong evidence was therefore demonstrated in favour of the need for preventative interventions. A common discussion point was late childhood as a key time for targeting preventative interventions and acknowledgement that universal interventions are typically not universally effective, with greater benefits being measured in those with greater needs at baseline (Dadds et al.,
1997; Horowitz et al.,
2007). Preventative interventions aimed at those with greater needs at baseline, where early or mild symptoms of a disorder are already present, have been categorised as ‘indicated’ (Neil & Christensen,
2009).

A viable intervention approach not yet investigated in the research literature is occupational therapy to promote mental health and reducing symptoms of mental ill-health in children. Occupational therapy’s unique contribution to health promotion includes: reduce risk factors and symptoms through engagement in occupation; providing skill development training in the context of everyday occupations; and providing training in adaptation to change and coping with adversity to promote mental health (not an exhaustive list) (AOTA Commission on Practice,
2001,
2008; Godfrey,
2000). Occupational therapists can assess how able a child is to participate in daily occupations outside of a standardised context and how frequently the child actually participates, and can use the child’s performance of developmentally appropriate occupations to promote health and wellbeing (Costello et al.,
2003; Cramm et al.,
2012; Zahn-Waxler et al.,
2000).

The need for research validating the effectiveness of occupational therapy in primary health has been identified as essential (AOTA Commission on Practice,
2001; Nicholson,
2011). A literature search found one article that explored the role of occupational therapy in promoting wellbeing in a population exposed to a common trauma i.e. child survivors of war (Simo-Algado et al.,
2002). To date, there is no evidence for the use of occupational therapy as an intervention to promote general mental health and increase self-esteem and participation in a primary health setting or preventative context.

### Aim and hypotheses

The aim of this study is to use the rigour of a cluster-randomised controlled trial to investigate the effectiveness of an indicated occupational therapy group intervention (Kia Piki te Hauora) at reducing symptoms of anxiety and depression and improving self-esteem and participation in children aged 11–13 years on completion of the intervention and the sustainability of any improvements after a follow-up period of 8–9 weeks.

#### Primary hypothesis

There will be a difference in post-intervention levels of child-rated anxiety between the intervention group and the waitlist control group.

#### Secondary hypotheses

There will be a difference in post-intervention levels of self-, parent- and teacher-rated symptoms of anxiety and depression, child self-esteem and participation in typical occupations between the intervention group and the waitlist control group.There will be a difference in self-, parent- and teacher-rated symptoms of anxiety and depression, child self-esteem and participation in typical occupations between post-intervention and 8 weeks follow-up.There will be a relationship between change in participant knowledge about occupations, health and wellbeing between pre- and post-intervention and change in the other outcome measures.

## Methods

### Trial design

This is a two-arm, pragmatic, cluster-randomised controlled trial in which schools are the unit of randomisation. The trial will employ an open-label, repeated measures, parallel and one-way crossover design. Children will be naturally clustered by school and this design will prevent contamination between trial arms (intervention and waitlist). One-way crossover will occur when children allocated to the waitlist crossover to start receiving the intervention after a set time. The trial has been approved by the New Zealand Health and Disability Ethics Committees (14/NTA/13) and is registered with the Australia/New Zealand Clinical Trials Registry (ACTRN12614000453684) http://www.anzctr.org.au/default.aspx.

### Study procedures

#### Setting

All schools in the Auckland region, providing mainstream education to children in Years 7 and 8 will be invited to participate through a notice in a national teaching magazine. In New Zealand, Years 7 and 8 cater to the needs of children aged 11–13 years. A stratified sample of 50 of those schools will be sent personal invitations to participate. Schools will be stratified by decile ranking proportionate to their representation nationally (i.e. low, medium, and high): decile ranks are a measure of the socio-economic population from which a school draws its students and affects their funding (Ministry of Education,
2014). Fourteen schools will be recruited with stratification targets of 4 for each of the low and high deciles, and 6 for the medium decile. Senior staff from schools expressing an interest will be offered a meeting with the lead researcher who will explain the study process and obtain consent. This process will be repeated until all 14 schools have been recruited.

#### Participants

A sample of 10–12 students aged 11–13 years at each of the enrolled schools will be recruited by senior personnel from the school (e.g. Special Education Needs Coordinator, Principal). Selection will be based on the school personnel’s judgement of the child presenting with early symptoms of anxiety along with symptoms of depression, low self-esteem and/or poor participation in typical occupations. Participant information sheets and parental consent forms will be sent home with the children and collected back in by school personnel. With parental or caregiver permission, the school will provide child and parent contact details to the researcher to facilitate follow-up and offer the opportunity for parents or caregivers to ask questions about the study. Children with signed parental consent will be invited to participate in the study and if they assent they progress to screening. Children will be included if they are:

Aged 11–13 years.Able to converse in basic English.A mainstream student (i.e. no intellectual disability).

Children will be excluded if their self-, teacher- or parent-report indicates suicidal or para-suicidal thoughts/behaviours or if they are already involved with secondary mental health services to address anxiety or depression. These children will be given information about relevant support services in their area and a referral made where appropriate.

### Intervention

The intervention is a manualised, occupational therapy group intervention: Kia Piki te Hauora (Uplifting our Health and Wellbeing). The intervention is designed to use engagement in developmentally appropriate activities to promote mental health and wellbeing by enabling students to understand the relationship between what they do and how they feel/think; to understand how activities in which they engage influence their identity, self-concept, health and wellbeing; to practice and develop strategies for overcoming difficult emotions; and to apply this knowledge in building and designing healthy routines, behaviours and habits in their day-to-day life that support self-esteem and participation (Table 
1). Group content includes: didactic activities (e.g. occupational analysis, fight-or-flight, relaxation techniques); peer exchange (e.g. occupational charades, brainstorming); direct experience (e.g. relaxation, games); and personal exploration (e.g. occupational analysis, pepeha^a^, activity scheduling). The intervention will run for 1 hour a week over a period of 8 weeks of a school term. Outcomes will be measured at the individual level although the intervention will be provided in a group context.

**Table 1 Tab1:** **Kia Piki te Hauora overview of content**

Session	Theme
1	Introduction
2	Sleep and rest occupations
3	Physical and active occupations
4	Communicating and occupations
5	Occupational disruption
6	Coping occupations
7	Values, identity and occupations
8	Closing and celebration

The intervention was developed following a consultation process with a panel of occupational therapists, cultural advisors, school personnel, children, the clinical experience of the first author ([name] et al.,
2013) and evidence of occupational therapy in different contexts. The theoretical knowledge underpinning the intervention is drawn from occupational therapy and science, interventions such as Lifestyle Redesign (Jackson et al.,
1998; Mandel et al.,
1999; Scott et al.,
2001) and Five Ways to Wellbeing (The New Economics Foundation,
2008,
2011). Occupational therapy interventions are based on the understanding that engagement in meaningful doing is important to maintain and restore health and to enable us to develop (Gitlin,
2013). Occupational science has provided a five-step approach for developing evidence-based practice that informs our understanding of the influence of interventions on an individual and their environment from an occupational perspective (Jackson et al.,
1998; Mandel et al.,
1999). This study attempts to contribute to that process in the development of a preventative occupational therapy intervention for children, similar to the Lifestyle Redesign programs. The Five Ways to Wellbeing are a set of five simple, evidence-based actions that can improve wellbeing in everyday life: connect, give, notice, keep learning and get active (The New Economics Foundation,
2011). These messages have been woven into the intervention content with an approach that is intended to empower the child to be informed when making decisions about their own occupations, health and wellbeing (Kitching,
1998; Tacker & Dobie,
2008).

#### Piloting of the intervention

The intervention has been piloted in clinical practice with two schools. Information was collected about how the intervention might work within a school environment; about children’s responses to the intervention content and outcome measures being taken; and to gain stakeholder feedback. Positive feedback was received from both students and school personnel with a number of modifications made to the programme as a direct result of this process.

#### Treatment fidelity

Treatment fidelity will be scored by the facilitator using a fidelity implementation checklist based on those designed and used by Forgatch et al. (
2005). The checklist records delivery of the intervention and student responsiveness per session. Each achieved item scores 1, giving a total possible score of 14 per group or 112 per cluster (Table 
2). Participant fidelity will be measured through attendance and completion of homework tasks.

**Table 2 Tab2:** **Intervention fidelity checklist**

Intervention component	Achieved (Y/N)
**Adherence**	
Objectives and plan posters up	Y/N
Key purpose identified (verbal)	Y/N
Activities conducted	Y/N
Materials used	Y/N
Key messages reviewed (quiz)	Y/N
**Duration and exposure**	
Between 55–60 minutes spent on session content	Y/N
**Quality of delivery**	
Facilitator comes prepared	Y/N
Facilitator encouraging and enthusiastic	Y/N
Explicit instructions given	Y/N
Constructive and positive feedback to students given	Y/N
Pacing and transitions effective	Y/N
**Programme specificity**	
Adheres to activities as designed	Y/N
Shows knowledge of content and intervention strategies	Y/N
**Student responsiveness**	
Most students are actively engaged or willingly compliant	Y/N
**Total score = total number of ‘Yes’s (max 14)**	

### Waitlist-control

The waitlist group will not receive any input during the parallel component of the trial and will only complete the baseline and post-intervention outcome measures. In the crossover component of the trial, the waitlist group will go on to receive the intervention as described.

### Outcome measures

Participants will complete all outcome measures on three or five occasions, depending on the arm of the trial to which they are allocated (Figure 
1).

**Figure 1 Fig1:**
[figure not shown]
**Participant flow through the study.**

#### Primary outcome measure

The primary outcome for effectiveness of this intervention is the participant’s self-rating of anxiety symptoms as assessed with the Multidimensional Anxiety Scale for Children – Short form (MASC-10) (Table 
3). The measurement taken 9 weeks after baseline will be the primary endpoint. The MASC-10 is the most widely used measure of anxiety in research with children and its psychometric properties have been well researched. Test-retest reliability of the MASC-10 is moderate to excellent and it has good reported internal consistency (Baldwin & Dadds,
2007; March & Sullivan,
1999; Muris et al.,
1998). Birmaher et al. (
1997) have demonstrated good discriminant validity. The MASC-10 has strong discriminant validity supported by correlation with the CDI (Myers & Winters) and SCARED (Muris et al.,
1998); it is sensitive to treatment effects and able to discriminate between anxious children and non-anxious children (Myers & Winters,
2002).

**Table 3 Tab3:** **Outcome measures**

Outcome measure	Rater	Instrument	Description
**Anxiety**	Child	Multidimensional Anxiety Scale for Children: Short form (MASC-10) (March, 1997)	Self-rated questionnaire with 10 items measuring the child’s thoughts and emotions, specifically related to anxiety.
	Parent	Revised Child Anxiety and Depression Scale – Parent report, short version (RCADS-PS) (Weiss & Chorpita, 2011)	Parent-report questionnaire with 25 items measuring their child’s anxiety and depression.
		Modification of original measure.	
	Teacher	School Anxiety Scale (SAS) (Lyneham et al., 2008)	Teacher-rated questionnaire with 16 items that measure the level of anxious behaviours a child is displaying.
**Depression**	Child	Children’s Depression Inventory – 2 (CDI-2) (Kovacs, 1992)	Self-rated scale with 10 items measuring the child’s mood, thoughts and presentation of depressive symptoms.
	Parent	Revised Child Anxiety and Depression Scale – Parent report, short version (RCADS-PS) (Weiss & Chorpita, 2011)	Described above.
		Modification of original measure.	
**Self-esteem**	Child	Rosenberg Self Esteem Scale (RSES) (Rosenberg, 1965).	Self-rated questionnaire with 10 items measuring the child’s thoughts about their own abilities and self-worth.
	Parent	Single Item Self-Esteem Scale (SISES) (Robins et al., 2001).	Single item parent-rated questionnaire that measures the parent’s general evaluation of the child’s self-esteem.
**Participation in daily occupations**	Child	Canadian Occupational Performance Measure (COPM) - modified (Law et al., 2005)	Measures self-reported ability to participate in daily activities and satisfaction with one’s ability to participate in those daily activities. Two chosen activities the individual would like to improve on from a menu of activities pertinent to the intervention goals.
	Parent	Canadian Occupational Performance Measure (COPM) - modified (Law et al., 2005)	Measures parent-report of their child’s ability to participate in the two daily activities chosen by their child (see above) and satisfaction with their child’s ability to participate in those daily activities.
**Life satisfaction and wellbeing**	Child	Wellbeing and life satisfaction questions (The Children’s Society, 2012)	Self-rated questionnaire with five items measuring a child’s sense of wellbeing and life satisfaction.
**Knowledge about occupations, health and wellbeing**	Child	Knowledge survey	Seven sets of two questions each week in multiple choice and True/False formats. Measures change in participant knowledge of concepts and strategies covered in the intervention.

#### Secondary outcome measures

In Table 
3 all secondary outcome measures are listed. Secondary outcomes include teacher- and parent-rated child symptoms of anxiety, symptoms of depression, self-esteem, participation in daily occupations, life satisfaction and wellbeing and knowledge about occupations, health and wellbeing.

#### Demographics

Socio-demographic data consisting of age, gender, ethnicity, and year of education will be collected at baseline.

### Sample size

A difference of ±5 in the *t-*score on the primary outcome measure (MASC-10) after an 8-week period can be considered clinically significant (March,
1997). To achieve a power of 80% at a significance level of 5%, 63 participants per study arm are required, a total of 126 children from 14 schools. This calculation is based on a sample size requirement for an individually randomised trial of 64 participants per arm, adjusted by a design effect of 0.98, which accounts for clustering and adjustment for baseline values. A target sample of 154 participants will be recruited to allow for possible 10% attrition.

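### The stated 80% power for 126 children in 14 schools makes no allowance for the few schools; on the plan's own design effect it is about 72–74%

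*Protocol article*

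**What the plan says.** The Sample size section of the protocol article takes a 5-point difference in the MASC-10 T-score as clinically significant and concludes: "To achieve a power of 80% at a significance level of 5%, 63 participants per study arm are required, a total of 126 children", to come from 14 schools. It gives the derivation as a "sample size requirement for an individually randomised trial of 64 participants per arm, adjusted by a design effect of 0.98", and says that this factor covers both clustering and adjustment for baseline. A target of 154 is then set to allow for 10% attrition.

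Trial design makes the school the unit of randomisation. Under Setting, "Fourteen schools will be recruited with stratification targets of 4 for each of the low and high deciles, and 6 for the medium decile". The randomisation section allocates schools within the three decile strata and aims for balance in each. The Statistical analysis section lists school decile as a covariate. The primary hypothesis is non-directional: "There will be a difference in post-intervention levels of child-rated anxiety between the intervention group and the waitlist control group".

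**The concern.** Clustering affects a power calculation in two ways. It changes the variance of the treatment contrast, which a design effect handles. It also limits the information available to estimate that variance, because between-school variation is estimated from 14 schools and not from 126 children. The second effect enters through the reference distribution: with 12 or 10 degrees of freedom the two-sided 5% critical value is 2.18 or 2.23, against 1.98 for 124. The printed derivation has a step for the first effect and none for the second.

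The power statement concerns the primary hypothesis. If it is too high, the risk of missing a difference that the plan itself calls clinically significant is larger than the 20% a reader would assume.

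**Working it through.** **Inputs from the Sample size section:** difference 5 points; 5% significance; 80% power; 64 per arm before adjustment; design effect 0.98; 126 children; 14 schools; target 154; attrition 10%.

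**Assumptions:** SD 10 and a two-sided test. Neither is printed. SD 10 is the usual T-score scaling, and two-sided testing fits the ± sign and the non-directional hypothesis. Together they return the plan's own 64. Seven schools per arm is also assumed, in line with 63 per arm at 126/14 = 9 children per school.

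**1. Reproduce the plan's figure.** Two-sample t-test, standardised difference 5/10 = 0.5, n = 64 per arm:
- noncentrality = 0.5 × √(64/2) = 2.828, on 126 df, gives power 80.1%; 63 per arm gives 79.5%, so 64 is the smallest adequate n.
- 64 × 0.98 = 62.72, rounded up to 63 per arm, or 126 in total.

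The stated figure is reproduced in full, with no step left for the number of schools.

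**2. Same inputs, between-school degrees of freedom.** With 63 per arm and design effect 0.98:
- standard error = 10 × √(2 × 0.98/63) = 1.764
- noncentrality = 5/1.764 = 2.835

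| Degrees of freedom | Critical value | Power | Difference detectable with 80% power |
|---|---|---|---|
| 124 (children) | 1.98 | 80.3% | 4.98 |
| 12 = 14 − 2 | 2.18 | 74.0% | 5.38 |
| 10 = 14 − 2 − 2 (three strata) | 2.23 | 72.4% | 5.49 |

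A simulation of the school-mean t-test (7 against 7 schools, 9 children each, intraclass correlation 0.02, 0.05 and 0.10, variance set so that the design effect is 0.98) gave 73.9–74.1% on 12 df. This step needs no assumed intraclass correlation, because 0.98 is held as printed.

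**3. The planned sample after attrition.** 154 × 0.9 = 138.6 children, or 9.9 per school. With 0.98 held, noncentrality = 0.5 × √(69.3/(2 × 0.98)) = 2.973, and power is 76.4% (10 df) or 77.9% (12 df).

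If the design effect has the form (1 + (m − 1) × ICC) × (1 − r²), it rises with the number per school, m. Here r is the baseline correlation, set for each assumed ICC so that the design effect is 0.98 at m = 9. The table also shows no attrition (m = 11):

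| Assumed ICC | Design effect, m = 9.9 | Power at 138.6 (10 / 12 df) | Design effect, m = 11 | Power at 154 (10 / 12 df) |
|---|---|---|---|---|
| 0.01 | 0.988 | 76.1% / 77.6% | 0.998 | 79.9% / 81.3% |
| 0.02 | 0.995 | 75.8% / 77.3% | 1.014 | 79.3% / 80.7% |
| 0.05 | 1.012 | 75.1% / 76.6% | 1.050 | 77.9% / 79.4% |
| 0.10 | 1.029 | 74.4% / 75.9% | 1.089 | 76.4% / 77.9% |

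With 0.98 held at all 154, power would be 80.6% (10 df) or 82.0% (12 df).

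**The case against.** **126 is not the sample planned for analysis.** This has force. The target of 154 loses about 15 children at 10% attrition, and falling to 126 would take 18% loss (1 − 126/154). The target therefore holds a margin of about 14 children over the 140 that 126/0.9 requires. The planned trial is some 2 to 6 points below 80%, not 6 to 8. But the article attaches the 80% to 126 children and offers the larger number only for attrition, and power at about 139 is still below 80%.

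**A reader might infer that no valid analysis could reach 80%.** The documents do not support that. If all 154 are analysed and the intraclass correlation is 0.01–0.02, power is about 81% on 12 df. The inputs behind 0.98 are not printed, so more favourable ones cannot be excluded.

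**A reader might also infer an arithmetic slip, or that every input used here is printed.** Neither is so. The multiplication is correct, and the fault is a missing allowance for few clusters. SD 10 and two-sided testing are inferences from the 64.

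**The article may leave the inputs to the full protocol.** That is right for the intraclass correlation and baseline correlation, and their absence is not part of this point. The point concerns a printed power whose derivation is printed beside it.

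**A mixed model with data-driven degrees of freedom could have more than 12.** That is possible when the estimated intraclass correlation is near zero, but the article specifies no such method and its power figure does not rest on one.

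**The data monitor may recommend sample size changes (Data management).** This limits the consequence but does not correct the figure. Nor does the figure bias any estimate or inflate the type I error.

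**Conclusion.** The point holds. On the article's own difference and design effect, 126 children from 14 schools give about 72–74% power, not 80%, so the risk of missing a 5-point effect is about 26–28%. The difference detectable with 80% power is 5.4–5.5 points, above the 5 points treated as clinically significant. At about 139 analysed, power is about 76–78% with 0.98 held and about 74–78% over the assumed intraclass correlations of 0.01–0.10. Reaching 80% needs nearly all 154 children analysed and a small intraclass correlation.

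These figures assume SD 10, a two-sided test, seven schools per arm, and a test against between-school variation on 12 df, or 10 after the strata. They also take the printed 0.98 as correct.

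**What to change.** In the Sample size section, restate the power using a t reference distribution on between-school degrees of freedom: about 72–74% at 126 analysed children and about 74–78% at about 139. Alternatively, state the difference detectable with 80% power, 5.4–5.5 T-score points at 126. In either case, give SD 10 and two-sided testing as assumptions.

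The cost is one paragraph and a slightly less favourable figure. Enrolment, the number of schools and the analysis need not change.
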